### Trial management

An independent Study Steering Group (SSG) will be established to monitor progress, advise the investigators in general scientific and management issues and ensure that there are no major deviations from the study protocol. The SSG will include an independent chair, and at least two other independent members with research experience with young people with mental health problems and/or self-harm. The SSG will also include two young people from the Oxford Health participation group. The SSG will meet at least once per year. The lead applicant will inform the SSG Chair who may call additional meetings when there are matters arising from the conduct or management of the trial that might require their advice

A Data Monitoring Committee was not convened as there was no panned interim analysis. Adverse events were reviewed by the SSG.

### Adverse event reporting and harms

For the purposes of this trial, adverse events are defined as increases in extent of self-harm or suicidal ideation regardless of whether they are casually related to the trial procedures. Serious adverse events are those requiring hospital admission. All adverse and serious adverse events will be reported to the project leader and will be reviewed by the SSC.

Clinicians will be requested to inform study researchers should a young person experience an adverse event during their participation in the study. At both follow-up visits, the young person (and parent if under 16) will be asked whether any adverse events have occurred and whether they think the study is having any negative effects on their mental health and self-harm frequency.

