
### Sample size

A 3-point difference on our primary outcome (RTSHIA) between treatment groups represents a clinically important difference.^35^ However, we propose to adopt a more conservative approach and will power the study to detect a moderate effect representing a 2-point difference. With an SD of 3.6, 90% power, alpha set at 0.05, we will require 69 participants per group.

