## Discussion

There is little research evaluating the effectiveness and cost-effectiveness of interventions in the treatment of self-harm in adolescents. Intervening with those who self-harm is important since self-harm during adolescence is a significant risk factor for future suicide attempts and completed episodes.^10 11^ The development of mHealth apps to support mental health interventions for adolescents offers a novel and accessible way of providing support at times of crisis. However, while technology offers many potential benefits, few apps to prevent self-arm have been developed and there is a lack of evidence regarding their efficacy, safety and acceptability.^25^

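### Hospital admission is the only criterion for a serious adverse event, so a death by suicide without admission would be classed as non-serious

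*Protocol article*

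**What the plan says.** The harms section of the protocol article sets a two-step rule, introduced as applying to this trial. First, "adverse events are defined as increases in extent of self-harm or suicidal ideation", whether or not trial procedures caused them. Second, "Serious adverse events are those requiring hospital admission". The second sentence is the whole of the seriousness definition.

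Reporting does not depend on that label: "All adverse and serious adverse events will be reported to the project leader and will be reviewed by the SSC". Events come to light in two ways. "Clinicians will be requested to inform study researchers should a young person experience an adverse event during their participation in the study", and the young person (with a parent if under 16) is asked about them at both follow-up visits.

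The Discussion states that "self-harm during adolescence is a significant risk factor for future suicide attempts and completed episodes".

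**The concern.** A seriousness definition should at least capture the worst outcomes foreseeable in the population. This trial enrols 12 to 17 year olds who have self-harmed at least twice in the past 12 months, and the article itself names suicide as a downstream risk. With hospital admission as the only criterion, an event that never leads to admission cannot be serious, even if that is because the young person died first.

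What is at stake is the meaning of the serious-event count. A reader of the results would expect a count of zero to mean that nobody died and nobody came close to dying. Under this rule it would mean only that no adverse event required admission.

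**Working it through.** No arithmetic bears on this point. The article's one design calculation, the sample size, does not enter it. The check is to apply the written rule to the kinds of event that can occur, and then to look for anything elsewhere that changes the answer.

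**Applying the rule.** The word *those* in the seriousness sentence refers back to adverse events, so an event must first be an increase in self-harm or suicidal ideation and must then require admission.

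| Event | Adverse event? | Serious under the rule? |
|---|---|---|
| Self-harm leading to admission | Yes, if an increase in extent | Yes |
| Death by suicide without admission | Yes, on an ordinary reading | No |
| Life-threatening self-harm that needed admission, which did not take place | Yes, on an ordinary reading | Depends on whether *requiring* means needing or receiving admission |
| Life-threatening self-harm treated in an emergency department, with no admission needed | Yes, on an ordinary reading | No |

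**Looking for a second criterion.** Trial management, Outcome measures, Economic analysis, Planned analysis and the Discussion were read for any mention of death, life-threatening events, lasting disability or medically important events as grounds for seriousness. None contains one, and none refers to a fuller definition elsewhere.

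**Is the event lost, or only mislabelled?** The reporting sentence covers adverse and serious adverse events alike. A suicide or a life-threatening episode that counts as an adverse event therefore goes to the project leader and on to the steering committee under either label. The rule changes how it is classified and counted, not whether it is reported.

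**Are the data there to separate emergency attendances?** Baseline and Economic analysis both describe a case-note review that picks up accident and emergency attendances after self-harm. Attendances without admission can therefore be counted from a source already planned, provided the extraction notes whether each one led to admission. The article does not say whether it does.

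**The case against.** The strongest reply is that this is a condensed article. It gives harms two short paragraphs, and a full list of seriousness criteria is commonly left to the full protocol. That would answer a complaint that something is missing. It does not answer this one, because the article states the rule as complete and the rule as stated is wrong. The full protocol may hold a wider definition, but nothing here points to one.

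A second reply is that *requiring* admission can mean needing it whether or not it took place. That stands in part: it would bring in some life-threatening episodes, which is why that half of the point is put only as a possibility. It does not rescue a death without admission.

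A third reply is that every adverse event is reported and reviewed, so only a label is at stake. This stands, and it limits the point to classification.

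A reader might go further and draw three stronger conclusions, which the article does not support:

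- **That serious harm would go undetected or unreviewed.** Clinicians are asked to report during participation, participants are asked at both follow-up visits, and all events go to review.
- **That oversight is defective.** Trial management says "A Data Monitoring Committee was not convened as there was no panned interim analysis" and "The SSG will meet at least once per year". But it gives adverse event review to a group with an independent chair and further independent members, and it lets the chair call extra meetings, so the yearly meeting is a minimum. One may prefer another arrangement, but this one is stated and workable.
- **That a claim of safety rests on a serious-event count by arm.** The article describes no such table. The abstract assigns safety to the interviews after use at 12 weeks, and the aims at the end of the Background are effectiveness, cost-effectiveness and acceptability.

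**Conclusion.** The definition is wrong as written. A death by suicide without admission is non-serious under it, and a life-threatening self-harm episode treated without admission may be, depending on how *requiring* is read. The consequence is confined to classification and to the serious-event count. The planned efficacy analyses and the sample size are untouched.

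The size cannot be put as a number, because the article gives no rate for deaths, life-threatening episodes or emergency attendances without admission. The number of events affected may be zero or very small, but each would be among the gravest the trial could record.

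The conclusion rests on two assumptions: that the seriousness sentence is meant as the full rule, as its wording indicates, and that a fatal or life-threatening episode would be treated as an increase in the extent of self-harm and so enter the adverse event record at all.

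**What to change.** Amend the seriousness definition so that any death and any life-threatening event count as serious alongside any event requiring hospital admission. Word it to stand on its own, so that a death need not first be judged an increase in self-harm before it can count. State whether *requiring* admission means needed or received.

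Separately, tabulate emergency attendances for self-harm that did not lead to admission, using the case-note review. Fix the period covered: Economic analysis gives baseline to 6 months, whereas the Follow-up section gives 12 weeks to 6 months. Confirm that the extraction records admission.

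These changes concern classification and reporting only. They cost a short amendment and one small table. The downside is that a few more events would be classed as serious. If the full protocol already has the wider definition, the article's sentence needs only to be brought into line with it.

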### Ethics and dissemination

Favourable ethical opinion for the research was obtained from the South Central—Oxford B NHS Research Ethics Committee (19/SC/0212) and was approved by the HRA and Health and Care Research Wales, prior to the recruitment of participants commencing at any NHS site. We will disseminate our findings to academics and researchers through high impact open access publications and through presentations at relevant academic and clinical conferences. Results will be made available to all participants after the completion of the study.

## Discussion

There is little research evaluating the effectiveness and cost-effectiveness of interventions in the treatment of self-harm in adolescents. Intervening with those who self-harm is important since self-harm during adolescence is a significant risk factor for future suicide attempts and completed episodes.^10 11^ The development of mHealth apps to support mental health interventions for adolescents offers a novel and accessible way of providing support at times of crisis. However, while technology offers many potential benefits, few apps to prevent self-arm have been developed and there is a lack of evidence regarding their efficacy, safety and acceptability.^25^

### Strengths and limitations

This is the first adequately powered RCT of a digital self-help app codesigned with, and used by, young people aged 12–17 years in receipt of specialist mental health services. This study will add to the evidence-base and will document the effectiveness and cost-effectiveness of adding a self-help app to usual care. If benefits are identified, BlueIce app can be widely made available to young people attending specialist CAMHS to provide help at times of distress.

As it is not feasible to blind participants to allocation, the research team is aware of the need to maintain equipoise and to present the two interventions to referring clinicians and participants in a balanced way. Researchers will remain blind to treatment arm and, if this is inadvertently broken, subsequent assessments will be conducted by another member of the research team. Similarly, following guidance from our participation group, those allocated to usual care will be provided with BlueIce at their final, 6-month assessment.

We have minimised the possibility of contamination between the trial arms. BlueIce is a prescribed app and is not freely available to download and use. Those allocated to UC+BI will be sent a single use download code. Once activated, BlueIce will automatically be installed on the participant’s smartphone and the access code will no longer work. Participants are, therefore, unable to share/pass the app/access code to others.

Finally, this project will evaluate the use of BlueIce as a prescribed app, used in conjunction with a specialist mental health intervention. Future research will be required to evaluate the use of BlueIce as a standalone, freely accessed self-help app or the mechanisms underpinning any effects.

### Trial status

Recruitment began in January 2020 and, pending COVID-19, will end around June 2022.

### Trial sponsor

Oxford Health NHS Foundation Trust. The sponsor will have no role in interpreting data, writing reports or decisions to publish findings.
